### Secondary Outcomes

Gambling and trading behaviors were assessed for frequency and intensity using items adapted from the EDADES survey [63] to capture gambling frequency and spending in both online and offline contexts. Trading behavior was assessed with items adapted from the study by Delfabbro et al [29], covering trading frequency, trading types, and frequency of monitoring financial markets. In the baseline and posttest assessments, these behaviors were measured retrospectively for the past year, while the follow-up covered the previous 3 months. Amateur or professional investment use was assessed with a dichotomous item (yes or no) regarding professional trading, as well as items on the use of broker platforms or apps.

Problem gambling was assessed using the 9-item Spanish version of the Problem Gambling Severity Index (PGSI) [66,67], categorizing participants into 4 groups: nonproblematic (PGSI=0), low-risk (PGSI=1‐2), moderate-risk (PGSI=3‐7), and problem gambling (PGSI≥8). Additionally, the Gambling Disorder Identification Test (GDIT) [68,69] was administered at follow-up as part of a planned validation process. The GDIT is a 14-item Likert scale instrument evaluating gambling behaviors, symptoms, and negative consequences. This scale allows for the classification of participants into the following categories: nongambling, recreational gambling, problem gambling, and pathological gambling (mild, moderate, or severe).

Disordered trading was measured with the Trading Disorder Scale [34], a validated 13-item instrument assessing problematic trading behaviors. The scale is based on research criteria proposed by Guglielmo et al [70], which are derived from selected *Diagnostic and Statistical Manual of Mental Disorders, Fifth Edition* (*DSM-5*) criteria for gambling disorder and internet gaming disorder [71] to conceptualize trading-related problems. This scale captures key aspects of behavioral addiction, such as tolerance, withdrawal, loss of control, craving, social impairment, and persistence despite negative consequences [34].

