### Other Measures

Gambling- and trading-related harms were measured using the Short Gambling Harm Screen [72], a brief 10-item binary-response tool adapted to capture financial, emotional or psychological, and relational harms from gambling and trading. Perceived self-efficacy to resist gambling and trading urges was measured using an adaptation of the Brief Situational Confidence Questionnaire [73], which has been psychometrically validated for gambling-related behaviors in an adult general population sample [74]. This adapted version includes 2 additional items assessing confidence in resisting the urge to gamble when faced with situations involving financial pressure or the influence of alcohol or drugs, complementing the original 8 items focused on unpleasant emotions, physical discomfort, pleasant emotions, social pressure, and tests of control. Peer and family gambling and trading behaviors were assessed through ad hoc items. These items inquired about friends’ and family members’ involvement in financial trading and gambling. Finally, a 5-point Likert scale was used to evaluate satisfaction with and usefulness of the online PNF intervention (only in intervention groups).

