During the evaluation of the PNF, observed variables will be controlled to ensure balanced baseline characteristics between control and experimental groups, thus confirming randomization integrity. Additionally, a comparative analysis will be conducted between participants who meet inclusion criteria (ie, engaging in gambling or trading activities in the past 60 days) and those who do not, assessing differences in sociodemographic variables, psychological distress, suicidal behavior, substance use, and gambling participation reported during eligibility assessment.

Questionnaires not previously validated in the Spanish population or for the constructs of interest will undergo psychometric evaluation, including item analysis, reliability, and validity testing. Item analysis will include item-test correlations, discarding items with discrimination indices below 0.30 [76]. Reliability analysis will be assessed using omega coefficients; a total omega ≥0.70 will be considered acceptable [77], while hierarchical omega will require a minimum of 0.50 per subscale [78]. Dimensionality and validity will be assessed through confirmatory factor analysis. Goodness-of-fit tests will be conducted, using the following indices and interpretations for the assessment of model fit: the comparative fit index, the relative goodness-of-fit index, the root mean square error, the Tucker-Lewis index, and the chi-square statistic corrected for degrees of freedom. A satisfactory model fit will be considered when the comparative fit index, Tucker-Lewis index, and relative goodness-of-fit index values are greater than 0.90; the root mean square error value is less than or equal to 0.05; and the chi-square statistic corrected for degrees of freedom values is close to 0 [79]. Measurement invariance will be tested across age, sex, and gambling or trading activity subgroups to confirm the stability of the factor structure across groups.

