## Results

The study was funded in December 2023. Baseline data collection was conducted between December 2024 and January 2025. A total of 1889 individuals completed the eligibility assessment, of whom 1112 (58.9%) met the inclusion criteria and were enrolled in the trial. The 12-week follow-up was finalized in March 2025, with 666 (59.9% retention) participants completing the final assessment. As of January 2026, data collection has been completed, and statistical analyses are ongoing. Primary results are expected to be published in March 2026.

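### The factor-analysis fit rule asks for a chi-square/df value near 0, but a correctly specified model has an expected value of 1

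*Protocol article*

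**What the plan says.** The last paragraph of the Data Analysis Plan covers questionnaires that lack validation in Spain or for the constructs of interest. For these, "Dimensionality and validity will be assessed through confirmatory factor analysis". Fit is then called satisfactory under a list of conditions joined by *and*:

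- CFI, TLI and "relative goodness-of-fit index values are greater than 0.90";
- "the root mean square error value is less than or equal to 0.05";
- "the chi-square statistic corrected for degrees of freedom values is close to 0".

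The first two conditions carry numbers. The third has a target but no cut-off. No other part of the article explains or modifies it. The Discussion presents the psychometric work on adapted measures as one of the study's contributions.

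**The concern.** A chi-square fit statistic is normally judged against its degrees of freedom, because that is its expectation when the model is right. Dividing by df puts the reference at 1. A rule that rewards values near 0 points at a region that a correct model almost never reaches, and which indicates no better structure than a value of 1 does.

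At stake is the stated standard for judging the adapted instruments. Taken at its word, the rule gives an unfavourable label to models that fit as well as sampling error allows. Taken loosely, it leaves the analyst to decide after seeing the data what counts as near zero. Neither is what a pre-stated criterion is for.

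**Working it through.** **Inputs from the article.** The Short Gambling Harm Screen is "a brief 10-item binary-response tool adapted to capture financial, emotional or psychological, and relational harms" (Other Measures). The Trading Disorder Scale is "a validated 13-item instrument assessing problematic trading behaviors", and "The GDIT is a 14-item Likert scale instrument" (both Secondary Outcomes). For sample size, "1112 (58.9%) met the inclusion criteria and were enrolled in the trial" (Results), and 666 completed the follow-up.

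**Assumptions.** The index is chi-square/df. The root mean square error is RMSEA. Each scale has one factor; the article gives no factor structure. It also does not list which instruments will be factor-analysed, so these three serve only to give realistic item counts.

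**Step 1: degrees of freedom.** A one-factor model with p items has df = p(p − 3)/2: 10 × 7/2 = 35, 13 × 10/2 = 65, 14 × 11/2 = 77.

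**Step 2: reference value.** Under a correct model the statistic T follows a chi-square distribution with df degrees of freedom. So E(T/df) = df/df = 1 and SD(T/df) = √(2/df). The plan's target near 0 cannot be reproduced as an expected value for any df.

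**Step 3: how often a correct model comes near 0.** The article gives no cut-off, so a range of possible ones is shown.

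| Items | df | SD of T/df | Central 95% range | P(< 0.25) | P(< 0.5) | P(< 0.75) |
|---|---|---|---|---|---|---|
| 10 | 35 | 0.239 | 0.59 to 1.52 | 0.0002% | 0.6% | 14.3% |
| 13 | 65 | 0.175 | 0.69 to 1.37 | < 0.0001% | 0.02% | 6.6% |
| 14 | 77 | 0.161 | 0.71 to 1.34 | < 0.0001% | 0.007% | 5.0% |

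For df 35 the central 90% range is 0.64 to 1.42. Even with a generous cut-off of 0.75, at least 85% of correct models miss it.

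**Step 4: simulation check.** For each setting, 1000 correct one-factor models were fitted by maximum likelihood to normal data, with loadings of 0.7 (assumed).

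| Items, N | Mean T/df | Share < 0.5 | Share < 0.25 | Share with RMSEA ≤ 0.05 |
|---|---|---|---|---|
| 10, 666 | 1.004 | 0.6% | 0 | 100% |
| 13, 666 | 1.001 | 0.1% | 0 | 100% |
| 10, 1112 | 1.011 | 0.4% | 0 | 100% |

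The harm screen has binary items, which these normal data do not mimic. A mean-adjusted chi-square for such items is scaled to the same expectation, so the reference stays at 1.

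**Step 5: relation to the RMSEA condition.** RMSEA² = max{0, (T/df − 1)/(N − 1)}. Setting RMSEA = 0.05 gives T/df = 1 + 0.0025 × (N − 1):

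- N = 666: 1 + 0.0025 × 665 = 2.66
- N = 1112: 1 + 0.0025 × 1111 = 3.78

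The limit lies above 1 at any N. Conversely, any T/df at or below 1 gives RMSEA = 0. A model that met the near-zero condition would therefore meet the RMSEA condition automatically, and the tolerance of 0.05 would never decide anything.

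**The case against.** **The phrase may not mean a ratio.** If it meant chi-square minus df, 0 would be the right reference. The wording does not exclude this, and the source cited for the criteria is not available here. Nothing in the text points that way, however, and division by df is the more natural sense of a statistic corrected for its degrees of freedom. This stands as a condition on the finding.

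**No cut-off is given, so no model fails mechanically.** This is correct. An analyst who takes the phrase to mean small would not mark down good models. The 0.5 used above is illustrative, which is why a range is shown. The reference value is still wrong, and the missing bound leaves the judgement open.

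**A reader might infer that the ratio and RMSEA conditions contradict each other.** They do not. Step 5 shows that the first is simply far stricter than the second on the same quantity. The result is redundancy, and the RMSEA condition itself contains no error.

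**A reader might infer that sound scales will be rejected and the validation conclusions will be wrong.** The article does not support that. It attaches no action to unsatisfactory fit, whereas for weak items it does name one (removal below a discrimination index of 0.30). It also does not say which scales the rule will reach. The self-efficacy questionnaire, for example, is described as already validated for gambling.

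**It is ancillary to the trial.** Also correct. The intention-to-change and intention-to-seek-treatment measures under Primary Outcomes are single items, which factor-analytic fit does not govern.

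**Conclusion.** The criterion is wrong as written on its natural reading: the reference for chi-square/df is 1, not 0. Read literally with a cut-off of 0.5, it would class more than 99% of correctly specified models at 35 or more degrees of freedom as unsatisfactory, although in simulation all of them met the plan's RMSEA condition. It also makes that RMSEA tolerance idle without contradicting it.

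This rests on three assumptions: the index is a ratio, the scales have one factor, and the phrase is applied literally. The expected value of 1 depends only on the first; the percentages depend on all three. The consequence is limited to the promised psychometric evaluation. Randomization, outcome definitions, power and the efficacy analysis are unaffected. It is a modest correction, but a clear one.

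**What to change.** Either of two changes to one sentence would do.

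1. Drop the chi-square/df condition and judge fit by RMSEA with its 90% confidence interval, CFI and TLI. This is the cleaner choice, since the ratio adds nothing to RMSEA once N is known.
2. Keep it, state that the reference is 1, and give an explicit upper bound. A bound tied to RMSEA 0.05 would be about 2.66 at N = 666 and 3.78 at N = 1112, which only restates the RMSEA condition; a tighter bound should be declared as such.

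If chi-square minus df was intended, the sentence should say so.

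The cost is one sentence, with no new data. The Results section reports that analyses were still ongoing in January 2026, so the rule can be corrected in the analysis documents and in the report. If any scale has already been judged under the present wording, its fit should be restated under the corrected rule.

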## Results

The study was funded in December 2023. Baseline data collection was conducted between December 2024 and January 2025. A total of 1889 individuals completed the eligibility assessment, of whom 1112 (58.9%) met the inclusion criteria and were enrolled in the trial. The 12-week follow-up was finalized in March 2025, with 666 (59.9% retention) participants completing the final assessment. As of January 2026, data collection has been completed, and statistical analyses are ongoing. Primary results are expected to be published in March 2026.

## Discussion

This study aims to address critical gaps in understanding emerging gambling and trading behaviors among young adults, a population that is increasingly involved in such activities, which have well-documented associations with psychological distress and gambling-related harm. Although generalizability may be influenced by the recruitment methodology, the online design of the study is particularly well suited to examining behaviors that occur primarily in digital contexts (eg, cryptocurrency trading and skin betting) [29,56,80] and enables timely and efficient assessment of motivational and behavioral outcomes over time [81].

To ensure data quality within this digital framework, sample characteristics were benchmarked against national reference data to contextualize representativeness [7]. Furthermore, to address limitations associated with self-reports, including social desirability bias, validated self-administered questionnaires and anonymized assessments were prioritized, and the Oviedo Infrequency Scale was included to detect and exclude random or dishonest responses. The use of multiple instruments for each measured variable will also allow for cross-verification, improving the reliability of the results. A key methodological strength is the use of an adapted Solomon 3-group experimental design, which enhances internal validity by allowing for the independent isolation of intervention effects from potential pretest sensitization.

This study represents a pioneering application of online PNF by extending it to the context of gambling-like practices, such as high-risk trading. To the best of our knowledge, this is one of the first randomized trials to assess the efficacy of PNF in increasing intention to change and help-seeking behaviors specifically within these emerging high-risk digital behaviors.

By examining the profiles of individuals who exhibit low motivation to seek help, the study also intends to provide insights that can contribute to the refinement of treatment and prevention strategies. However, several limitations should be acknowledged. First, longitudinal studies using online panels are susceptible to high attrition rates. To mitigate this, a conservative oversampling strategy (assuming 50% loss to follow-up) was used, and missing data will be handled via generalized linear mixed models. Second, as the sample is restricted to Spanish residents, cross-cultural generalizability may be limited. Finally, given the novelty of behaviors such as cryptocurrency trading, some measures were adapted ad hoc. Rigorous psychometric analyses are planned to validate these instruments as part of the study’s contributions.

Despite these limitations, findings may inform regulatory policies for trading platforms and gambling-like activities within video games to better protect vulnerable users. Excessive engagement in these activities has been associated with other addictive behaviors, such as disordered gambling and substance use, as well as emotional difficulties [82]. Furthermore, increased engagement in financial markets has been linked to rising suicide rates among both amateur and professional investors [70]. Consequently, the outcomes of the study are expected to advance public health by elucidating the psychological and social consequences of these converging behaviors and supporting the development of effective, scalable interventions aimed at reducing harm and facilitating help seeking in this population.
